### 2.8. Statistical analysis

The “Full Analysis Set” is defined as the population that excludes study participants for whom no data on the maximum TP value are available. Analyses of the primary and secondary endpoints will be performed using the full analysis set.

All analyses will be performed after the data for all endpoints have been collected, reviewed, and fixed.

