#### 2.5.1. Method of TP measurement.

After the participants are fully informed, TP is measured 3 times at each evaluation point by a TP measurement device (JMS Tongue pressure measurement device. JMS Co., Ltd.), and the maximum TP values are recorded. After treatment, the change in TP value is analyzed. If TP measurement is impossible, it is recorded as “Impossible” accompanied by a description of the reason.

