### 2.7. Sample size consideration

The study aims to enroll 40 patients with OPC or HPC who will be treated with CRT or RT over 4 years. The target number of cases was set based on feasibility, given that approximately 12 patients are treated annually with these therapies at the institution. If the average ± SD expected to change in the primary endpoint maximum TP is estimated to be 15.0, the width of the 95% confidence interval (CI) will be appropriately 4.0 ± 2.0 based on a previous study.

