#### 2.8.1. Primary endpoint.

The average and 95% CI of the changes in the maximum TP value from baseline 3 months after RT will be analyzed as the primary endpoint. Moreover, the ratio of patients with “Impossible” will be calculated.

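### The 3-month mean change covers only patients whose tongue pressure can still be measured, so it probably understates the decline; the 'Impossible' ratio discloses this but does not correct it

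*Protocol article*

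**What the plan says.** All references are to the protocol article.

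- **Recording (2.5.1).** TP is measured three times per visit and the maximum is kept. "If TP measurement is impossible, it is recorded as" 'Impossible', together with the reason.
- **Primary analysis (2.8.1).** The planned result is "The average and 95% CI of the changes in the maximum TP value from baseline 3 months after RT". The proportion of patients recorded as 'Impossible' is reported as well. Section 2.8.2 repeats both for the other visits.
- **Analysis set (2.8).** The full analysis set (FAS) "is defined as the population that excludes study participants for whom no data on the maximum TP value are available". It does not say at which visit. "Analyses of the primary and secondary endpoints will be performed using the full analysis set".
- **Discontinuation (2.4).** A patient whose TP becomes difficult to measure during or after treatment, through progression or adverse events, meets a discontinuation criterion.
- **Eligibility (2.3).** Patients who cannot hold the probe in position or press on it are not enrolled.
- **Size (2.7).** "The study aims to enroll 40 patients with OPC or HPC", a number set on feasibility.

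**The concern.** A word cannot be averaged. As written, the primary estimate is therefore the mean change among patients still measurable at 3 months, although it is described as the change in the trial population. Section 2.3 means that everyone enrolled should be measurable at entry, so a later 'Impossible' is mostly a new event. Section 2.4 names progression and adverse events as its causes. The introduction lists pain, mucositis and loss of tongue volume among the radiotherapy effects that impair swallowing. Patients who leave the mean for these reasons plausibly have greater loss of function than those who stay.

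What is at stake is the quantity the trial exists to estimate. The CI around the mean reflects sampling error only and makes no allowance for this selection. The TP–Hyodo correlation and the mean TP in the dysphagia group (2.8.2) also need a numeric TP, so they lose the same patients.

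The ratio that should reveal the problem is itself loosely fixed. If a patient is discontinued during radiotherapy under section 2.4, it is unclear whether that patient is still counted as 'Impossible' at 3 months.

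**Working it through.** **1. Inputs.** From section 2.7: n = 40, and a figure of 15.0 whose wording ("If the average ± SD expected to change in the primary endpoint maximum TP is estimated to be 15.0") does not say whether it is a mean or an SD. I take it as the SD. The documents give no expected 'Impossible' share and no TP change for such patients, so both are assumed below.

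**2. The plan's own precision figure.** Section 2.7 says "the width of the 95% confidence interval (CI) will be appropriately 4.0 ± 2.0 based on a previous study".

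- Half-width = 1.96 × 15/√40 = 4.65 (4.80 with the t quantile).
- Full width = 9.30 (9.59 with t).

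The stated width of 4.0 is not reproduced. That is a separate matter; here 4.65 serves only as a yardstick.

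**3. Shift from leaving out the unmeasurable.** Let q be the share unmeasurable, and d the amount by which their unobserved mean loss exceeds that of measurable patients. The mean over everyone is (1 − q) × measurable mean + q × unmeasurable mean, so:

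measured-only mean − mean over everyone = q × d, towards less loss.

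| q (assumed) | d = 5 | d = 10 | d = 15 | d = 20 |
|---|---|---|---|---|
| 10% | 0.5 | 1.0 | 1.5 | 2.0 |
| 20% | 1.0 | 2.0 | 3.0 | 4.0 |

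The range is 0.5 to 4.0 units, or 11% to 86% of the half-width (0.5/4.65 and 4.0/4.65).

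**4. Is d = 5 to 20 reasonable?** If change is normal with SD 15 and unmeasurability follows a latent normal variable with correlation ρ to the change, the shift is ρ × 15 × φ(z)/(1 − q), where φ(z) is the normal density at the q quantile.

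- q = 10%, ρ = 0.5: 0.5 × 15 × 0.1755/0.9 = 1.46, so d = 1.46/0.10 = 14.6.
- q = 20%, ρ = 0.5: 0.5 × 15 × 0.2800/0.8 = 2.62, so d = 2.62/0.20 = 13.1.

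A moderate correlation falls inside the range. With an assumed true mean of −4, simulated coverage of the nominal 95% interval was about 91% and 83% in these two cases.

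**5. Bounding case.** If exactly the worst patients are the unmeasurable ones (ρ = 1), the shifts are 2.92 (q = 10%) and 5.25 (q = 20%). With a true mean of −4 the measured-only means are −1.1 and +1.2, with simulated coverage of about 75% and 28%. This is a limit, not an expectation.

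**6. Precision.** With 36 or 32 measured patients the half-width grows only from 4.65 to 4.90 or 5.20. Bias is the larger problem, not lost precision.

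**7. The ratio.** If the FAS keeps anyone with at least one TP value and all 40 are measurable at baseline, 4 later 'Impossible' patients give 4/40 = 10%, with or without the FAS restriction. The count matters more. Suppose 8 of 40 become unmeasurable and 4 of them, discontinued during radiotherapy, are dropped from the 3-month tally. The ratio is then 4/36 = 11.1% instead of 8/40 = 20.0%. Sections 2.4 and 2.5.1 together allow either figure.

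**The case against.** The strongest reply is that the plan does not hide the loss. It foresees unmeasurable TP, records the reason, and reports the frequency beside the mean at every visit. For a descriptive single-arm study with no hypothesis test or success threshold, a mean among measurable patients plus the proportion not measurable is a recognisable two-part presentation. This stands, and it is why the planned mean can be kept. It does not answer the point that the mean is not labelled as conditional, or that its CI ignores the selection.

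Second, no passage says that 'Impossible' means the largest TP loss. Section 2.5.1 allows any reason, and section 2.3 shows that holding the probe also depends on the front teeth. This also stands: the direction is likely, not proven, and only losses due to adverse events or progression should be treated as bad outcomes.

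Third, the statistical analysis plan is not shown and may contain sensitivity analyses. Their absence from an article is no finding. The point rests on what the article does fix: a plain average, a coding that cannot enter it, and an unclear link to discontinuation.

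A reader might infer two stronger things that the documents do not support:

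- **That the FAS removes never-measurable patients from the 'Impossible' ratio.** Section 2.3 largely prevents such patients from being enrolled.
- **That the 3-month ratio is 0% by construction, because 'no data' means no 3-month value.** The wording does not exclude this, but section 2.8 defines one FAS for all endpoints, and a planned 'Impossible' ratio would then be pointless. The natural reading is no TP value at all; a clarifying phrase suffices.

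**Conclusion.** The concern holds in a limited form. As written, the primary analysis estimates change among patients still measurable at 3 months and probably understates TP decline. The ratio beside it discloses the loss without correcting the mean or its CI.

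The size cannot be determined from the documents. Under assumed shares of 10–20% and an excess unseen loss of 5–20 units, the shift is 0.5 to 4.0 TP units against a half-width of about 4.65, the latter with n = 40 and 15.0 read as the SD. A reader might take a reversed sign or coverage near 28% as the expected result. Those figures need exactly the worst 20% to be missing and an assumed true mean of −4, so they are a bound only.

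This is a worthwhile clarification with one added analysis, not a defect that invalidates the plan.

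**What to change.** 1. **Keep the planned mean and 95% CI**, labelled as the change among patients measurable at that visit.
2. **Pre-specify a companion analysis at each visit** that ranks 'Impossible' due to adverse events or progression as the worst outcome, and report the median change with a rank-based CI. With 40 patients the order-statistic interval runs from the 14th to the 27th ranked value (exact coverage 96.2%). Both limits therefore stay numeric while fewer than 14 patients are ranked worst. The median is a different quantity from the mean, so it supplements the mean and does not replace it. 'Impossible' for other reasons is not ranked worst.
3. **State the FAS** as all eligible enrolled patients with a baseline TP.
4. **State the ratio's denominator** as all enrolled patients due at that visit, including those discontinued because TP became unmeasurable.
5. **Reconcile sections 2.4 and 2.5.1** so that, whatever discontinuation rule stands, these patients are counted.

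A repeated-measures model may be added so that all visits draw on a consistent set of patients. It relies on missingness at random and does not remove informative loss, so it cannot replace step 2.

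The cost is mainly wording. Section 2.5.1 already requires the reason to be recorded, though for patients discontinued under section 2.4 that must be confirmed. The price is one extra reported analysis and a decline that may look larger. The change should be made before the data are fixed for analysis.

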#### 2.8.1. Primary endpoint.

The average and 95% CI of the changes in the maximum TP value from baseline 3 months after RT will be analyzed as the primary endpoint. Moreover, the ratio of patients with “Impossible” will be calculated.

#### 2.8.2. Secondary endpoint.

The average and 95% CI of the changes in the maximum TP value from baseline during RT, as well as 0, 1, and 6 months after RT will be analyzed as secondary endpoints. The ratio of patients with “Impossible” will be calculated as well.The change in the Hyodo score between the baseline and each evaluation point will be analyzed. The averages and 95% CI for the changes will be calculated. Moreover, the scatterplot and Pearson correlation coefficient between the Hyodo score and maximum TP value will be calculated.Dysphagia was evaluated based on the findings of VF at each evaluation point and the ratio of dysphagia among all participants, and the 95% CI of that will be calculated. Moreover, for participants in the group with dysphagia, the average and the 95% CI of both the maximum TP values and Hyodo score will be calculated.

For all the above endpoints, subgroup analyses will be conducted by subject characteristics (e.g., background information) to explore factors that may be useful in determining future research and treatment strategies.

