## Abstract

**Methods and Analysis::**

This ELEVATE trial is a prospective, single-center, single-arm, non-blind, non-randomized trial to evaluate the usefulness of a TP measurement device for dysphagia associated with the treatment of HNC. Eligible participants include patients with oropharyngeal or hypopharyngeal cancer (HPC) undergoing RT or chemoradiotherapy (CRT). The TP measurements are conducted before, during, and after RT. The primary endpoint is the change in the maximum TP values from before RT to 3 months after RT. Moreover, as secondary endpoints, the correlation between the maximum TP value and the findings of video-endoscopic and video-fluoroscopic examinations of swallowing will be analyzed at each evaluation point, as well as changes in the maximum TP value from before RT to during RT and at 0, 1, and 6 months after RT.

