#### 2.5.2. Data collection.

Patient data will be collected before, during, and after RT, and at 0, 1, 3, and 6 months after the final date of RT (Table 1). TP measurement and VE will be conducted before, during, and after RT and 0, 1, 3, and 6 months after the final date of RT. VF will be conducted before and after RT and at 1, 3, and 6 months after the final date of RT.

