#### 2.5.3. Evaluation of VE.

The findings of the VE will be evaluated by the Hyodo score.^[25,26]^

The Hyodo score is defined as follows:

I.The salivary pooling degree at the vallecula and piriform sinuses.0:No pooling1:Pooling at the only vallecular.2:Pooling in the vallecula and piriform sinuses, but no penetration into the larynx.3:Pooling in the vallecula and piriform sinuses and penetration into the larynx.
II.The glottal closure reflex induced by touching the epiglottis or arytenoid.0:Marked reflex by 1 touch.1:Slow and/or weak reflex by 1 touch.2:Reflex by 2 or 3 touches.3:No reflex despite several touches.
III.The location of the bolus at the swallowing reflex initiation as assessed by “white-out” timing.0:Pharyngeal.1:Vallecula.2:Piriform sinuses.3:No swallowing reflex.
IV.The extent of pharyngeal clearance after blue-dyed water is swallowed.0:No residue.1:Pharyngeal residues remain but are absent after 2 or 3 swallows.2:Pharyngeal residues remain but there is no penetration into the larynx.3:Pharyngeal residues remain and there is penetration into the larynx.

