#### 2.6.2. Secondary endpoint.

The secondary endpoints are listed as follows:

Changes in the maximum TP value from baseline to during RT as well as at 0, 1, and 6 months after RT. We performed the same analysis for the primary endpoint for each evaluation time.The findings of VE by the Hyodo score at each evaluation point.The findings of VF at each evaluation point.

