## 3. Discussion

The primary objective of this trial was to evaluate the usefulness of the TP measurement device for dysphagia in patients with HNC. The tongue plays a significant role in the oral stage of swallowing, and a decrease in TP may result in dysphagia.^[6–9]^ Therefore, maintaining TP will help prevent dysphagia; thus, better rehabilitation programs for dysphagia have been sought. Currently, a TP measurement device is generally used as a method of measuring TP.^[22]^ In the neurological field, the evaluation of dysphagia by a TP measurement device has already been established, and the correlation between lower TP and dysphagia has been clarified.^[5,18,19]^ However, the utility of assessing dysphagia using TP in patients with HNC has not yet been established. Despite that head and neck tumors often affect swallowing due to being in the oral cavity, pharynx, and larynx, there are currently limited methods for assessing dysphagia associated with HNC treatment.

In clinical practice, VE and VF are usually performed to evaluate dysphagia, and their utility has been established.^[23,24]^ However, these examinations carry a significant risk; therefore, they can cause AEs such as aspiration, pneumonia, and allergy to the contrast medium. Moreover, the VE and VF require practical clinical techniques. Therefore, this trial aimed to investigate the usefulness of evaluation by measuring TP for dysphagia related to HNC treatment.

In this trial, we evaluated the changes in TP affected by RT, since muscle damage by RT has already been reported and decreased TP could result in dysphagia in HNC patients.^[17]^ Thus, this study will include patients with OPC or HPC, in whom the tongue is exposed to radiation during treatment. As TP and swallowing function can be affected by the tumor itself, patients with oral cancer were excluded. Additionally, patients with laryngeal cancer were excluded because the radiation field for laryngeal cancer does not adequately include the tongue. The usefulness of TP measurement as the primary endpoint in HNC patients will be demonstrated. Additionally, the correlation between the change in TP and VE findings, as well as VF, will be analyzed as the secondary endpoint.

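### The correlation between tongue pressure and swallowing findings is defined differently in the Abstract, section 2.8.2 and the Discussion, and the VF correlation has no planned analysis

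*Protocol article*

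**What the plan says.** Four places in the protocol article bear on this analysis.

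- **Abstract, Methods and Analysis.** Among the secondary endpoints is "the correlation between the maximum TP value and the findings of video-endoscopic and video-fluoroscopic" "examinations of swallowing will be analyzed at each evaluation point". The quantity is the TP level, the references are VE and VF, and there is one analysis per evaluation point.
- **Section 2.6.2.** The VE endpoint is "The findings of VE by the Hyodo score at each evaluation point". VF findings are listed in the same way. No correlation appears as an endpoint.
- **Section 2.8.2.** The only coefficient is in this sentence: "the scatterplot and Pearson correlation coefficient between the Hyodo score and maximum TP value will be calculated". For VF the section plans the proportion with dysphagia and, within the dysphagia group, the means of maximum TP and Hyodo score with 95% CIs.
- **Section 3, Discussion.** Here "the correlation between the change in TP and VE findings, as well as VF, will be analyzed as the secondary endpoint".

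On the scale, section 2.5.3 says "The findings of the VE will be evaluated by the Hyodo score" and sets out four items, each graded 0 to 3. It states neither a total nor a range. On timing, section 2.5.2 says "TP measurement and VE will be conducted before, during, and after RT and 0, 1, 3, and 6 months" after RT. The notes to Table 1 define six windows.

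**The concern.** The trial's stated aim is to show that the TP device is useful for assessing dysphagia. The primary endpoint, a mean change in maximum TP, does not relate TP to swallowing at all. The correlation with VE is the only planned coefficient of association between TP and a reference examination. The mean TP in patients with VF-defined dysphagia comes near, but no comparison with patients without dysphagia is planned.

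A level correlation asks whether patients with low TP swallow worse at a given visit. A change correlation asks whether a fall in TP goes with a worsening of swallowing. A device could do well on one and fail on the other. If the text supports both, and supports a VF correlation in two places but not in the analysis section, the result that is reported can be picked once the data are known, and a reader cannot tell which was intended.

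**Working it through.** **1. The statements side by side**

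| Place | TP quantity | Against VE | Against VF | Time point |
|---|---|---|---|---|
| Abstract | level | yes | yes | each evaluation point |
| 2.6.2 | no correlation listed | – | – | – |
| 2.8.2 | level | yes (Hyodo, Pearson) | no correlation | not given for the coefficient |
| Discussion | change | yes | yes | not given |

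The Discussion also leaves open whether the change in TP is to be set against the Hyodo score at a visit or against its change.

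**2. How many analyses fit the text**

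Six windows have both TP and VE: before RT, during RT, and 0, 1, 3 and 6 months after. That allows 6 level coefficients and 6 - 1 = 5 change-from-baseline coefficients. VF is not scheduled during RT in section 2.5.2, so the Abstract's statement cannot hold for VF at every one of the six windows.

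**3. Level and change need not agree**

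Assume equal variances at two visits, same-visit TP–Hyodo correlation r, cross-visit TP–Hyodo correlation c, and between-visit correlations a (TP) and b (Hyodo). The change-versus-change correlation is (r - c) / √((1 - a)(1 - b)). Take r = -0.4 and a = b = 0.5 (assumed).

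- With c = -0.4: (-0.4 + 0.4) / 0.5 = 0.
- With c = -0.2: (-0.4 + 0.2) / 0.5 = -0.4.

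The same level correlation is compatible with no change correlation or with one of equal size.

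**4. Precision with 40 patients**

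The protocol gives no target correlation, so there is no figure to reproduce. The Fisher-z 95% limits are tanh(atanh(r) ± 1.96/√(n - 3)). For n = 40 the margin is 1.96/√37 = 0.322.

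- r = -0.3: atanh = -0.310, limits -0.632 and 0.013, giving -0.56 to 0.01.
- r = -0.4: atanh = -0.424, limits -0.746 and -0.101, giving -0.63 to -0.10.

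Fewer pairs widen this. At n = 30, r = -0.3 gives -0.60 to 0.07.

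**5. Pearson against Spearman**

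If the four items are summed, the range is 0 to 4 × 3 = 12. Simulated means for n = 40 (2,000 runs per scenario, item cut-points assumed):

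| Latent correlation | Scores | Pearson | Spearman |
|---|---|---|---|
| -0.3 | skewed to 0 | -0.218 | -0.217 |
| -0.3 | mid-range | -0.265 | -0.254 |
| -0.5 | skewed to 0 | -0.365 | -0.367 |
| -0.5 | mid-range | -0.443 | -0.426 |

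The largest gap is below 0.02, and there Pearson is the larger in size. A separate simulation with a floor-heavy score and latent correlation -0.45 gave Pearson -0.35 to -0.39 and Spearman -0.37 to -0.41, again about 0.02 apart.

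**6. Only if visits were pooled**

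Pooling would give 40 × 6 = 240 pairs. With the same within-patient ICC in both measures (assumed), the design effect is 1 + 5 × ICC². Simulation under no association gave false rejection rates of about 10%, 19% and 29% at ICC 0.3, 0.5 and 0.7, against a nominal 5%. For r = -0.4 the interval would shrink from (-0.63, -0.10) to (-0.50, -0.29). One coefficient per visit stayed at about 5%.

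**The case against.** The strongest reply is that the article is a condensed text, that the Abstract settles the timing, and that a descriptive coefficient shown with its scatterplot is ordinary practice. Much of this stands.

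- **Pooling.** A reader might infer from the missing time point in 2.8.2 that six visits per patient are to be correlated as independent pairs. The documents do not say so. The Abstract states "will be analyzed at each evaluation point", which gives one pair per patient per coefficient and no clustering. Nor is a test or interval planned for the coefficient, so the error rates in step 6 describe an analysis that the plan never states.
- **Pearson as an error.** A reader might infer that Pearson is invalid because of a floor at zero. The exclusions cover dysphagia from past HNC treatment and severe dysphagia from central disease. They do not exclude dysphagia from the present tumour, and five of the six windows fall during or after RT. The Introduction says about half of patients develop dysphagia. A heavy floor is therefore an assumption, and the numerical effect is small in any case.
- **Missing detail.** An interval for a descriptive coefficient may well be in an analysis plan that is not shown. Still, 2.8.2 attaches 95% CIs to the TP changes, the Hyodo changes, the dysphagia proportion and the group means, and is silent only here.

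None of this answers the contradiction. Condensing a text does not turn a level into a change, and it does not explain why VF is correlated in two places and not in the analysis section.

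**Conclusion.** The point holds as an inconsistency in what is to be analysed. The TP quantity differs between the Abstract and 2.8.2 (level) and the Discussion (change). The VF correlation stated in the Abstract and Discussion has no counterpart in 2.8.2, and 2.6.2 lists no correlation. This rests on wording alone and needs no assumption.

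Its size is moderate. The primary endpoint is untouched, but the analysis nearest the trial's aim is left open among as many as eleven VE coefficients (6 + 5), each with a wide interval at 40 patients. The choice of Pearson is a lesser matter of preference, worth about 0.02. Neither it nor the pooling figures should be cited as a fault in the plan; the pooling figures rest on assumed ICCs and on a reading that the Abstract speaks against.

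**What to change.** Settle the following before the data are fixed and analysed:

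1. In the Abstract, 2.8.2 and the Discussion, name the same quantities: maximum TP against the Hyodo score at each evaluation point, and change in maximum TP against change in Hyodo score from baseline. List them in 2.6.2.
2. State that each coefficient uses one pair per patient and is reported with a 95% CI.
3. Report Spearman's coefficient with or instead of Pearson's, because the items are ordered grades, and state that the four items are summed if that is meant.
4. For VF, either plan an association, for example maximum TP in patients with and without VF-defined dysphagia at each visit where VF is scheduled, or remove the VF correlation from the Abstract and Discussion.
5. If one estimate across visits is wanted, use a model with a patient random effect.

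The cost is a few sentences and slightly more analysis. No new data are needed.

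### The VF analysis in section 2.8.2 summarises TP and Hyodo score only in participants with dysphagia, so as specified it cannot give the TP-VF association that the abstract and discussion promise.

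*Protocol article*

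**What the plan says.** The protocol article describes the TP-VF analysis in three places.

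- **Abstract, Methods and Analysis.** The secondary aims are introduced as follows: "the correlation between the maximum TP value and the findings of video-endoscopic and video-fluoroscopic examinations of swallowing will be analyzed at each evaluation point".
- **Section 3, Discussion.** The aim returns in terms of change: "the correlation between the change in TP and VE findings, as well as VF, will be analyzed as the secondary endpoint".
- **Section 2.8.2.** For endoscopy (VE), "the scatterplot and Pearson correlation coefficient between the Hyodo score and maximum TP value will be calculated". For VF there are two steps. First, a proportion with its 95% CI: "Dysphagia was evaluated based on the findings of VF at each evaluation point and the ratio of dysphagia among all participants". Second, a summary limited to one group: "for participants in the group with dysphagia, the average and the 95% CI of both the maximum TP values and Hyodo score".

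The closing sentence of section 2.8.2 adds that "subgroup analyses will be conducted by subject characteristics (e.g., background information" are the basis for exploratory subgroups; VF status is not named there.

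Section 2.5.4 lists the VF features to be described and says that VF evaluation is not yet established. It gives no VF score and no cut-off for dysphagia.

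**The concern.** The discussion states the trial's primary objective as the usefulness of the TP device for dysphagia. The primary endpoint is the change in TP alone, so any evidence that TP tracks swallowing function has to come from the secondary analyses against VE and VF. For VE the plan has an association analysis. For VF it describes one side of a comparison and omits the other.

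A mean TP in patients with dysphagia cannot be read as low or high without the mean in patients without it. If section 2.8.2 is followed as written, the trial will finish without the VF half of an association that it twice announces.

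**Working it through.** The documents give no figure for the TP-VF association, so there is none to reproduce. The check is in three steps.

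**1. Promised against specified**

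| Comparison | Promised (abstract, discussion) | Specified (section 2.8.2) |
|---|---|---|
| TP with VE | Correlation | Scatterplot and Pearson coefficient with the Hyodo score |
| TP with VF | Correlation | Proportion with dysphagia; mean TP and Hyodo score in the dysphagia group only |

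The other numerical TP summaries in sections 2.8.1 and 2.8.2 are mean changes from baseline over the full analysis set. They are not TP levels at the visit, so the mean in the group without dysphagia cannot be obtained from them by subtraction.

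**2. Do the two VF outputs fix an association?**

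Let m1 and m0 be mean TP with and without VF dysphagia, p the proportion with dysphagia and s the within-group SD. The point-biserial correlation is

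r = (m1 - m0) × √(p(1 - p)) / √(s² + p(1 - p)(m1 - m0)²)

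Inputs: N = 40 is the target in section 2.7. The rest are assumed for illustration: 20 with dysphagia (p = 0.5), m1 = 25, s = 8. The planned outputs report p and m1 with its CI. The unreported m0 is varied:

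| m0 | m1 - m0 | r |
|---|---|---|
| 15 | +10 | 10 × 0.5 / √(64 + 25) = +0.53 |
| 20 | +5 | 5 × 0.5 / √(64 + 6.25) = +0.30 |
| 25 | 0 | 0.00 |
| 30 | -5 | -0.30 |
| 35 | -10 | -0.53 |

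With 10 or 30 patients in the dysphagia group, p(1 - p) = 0.1875 and the range is +0.48 to -0.48. The two planned VF outputs are the same in every row of the table, so they fix neither the sign nor the size of r.

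**3. Precision of the missing contrast**

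Half-width of the 95% CI for a difference in means = t(0.975, 38 df) × SD × √(1/n1 + 1/n0), with t = 2.024. The SD of 10 and the splits are assumptions, and all 40 are taken as evaluable. The even split follows the introduction's statement that about half of patients with head and neck cancer develop dysphagia from radiotherapy.

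| Split (with / without) | SD 10 | SD 15 (× 1.5) |
|---|---|---|
| 20 / 20 | 2.024 × 10 × 0.316 = 6.4 | 9.6 |
| 16 / 24 | 2.024 × 10 × 0.323 = 6.5 | 9.8 |
| 12 / 28 | 2.024 × 10 × 0.345 = 7.0 | 10.5 |

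Fewer evaluable patients would widen these. The protocol foresees both discontinuation and TP readings recorded as impossible.

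**The case against.** The strongest reply is that this is one part of a secondary endpoint in a descriptive single-arm study, that the article condenses a fuller protocol, and that the abstract and discussion do say the correlation will be analysed. The first part stands and sets the severity. The rest does not remove the point: section 2.8.2 does not leave the VF analysis to another document. It states a particular analysis, gives a coefficient for VE beside it, and the VF analysis it states does not yield what is promised elsewhere.

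Four stronger readings are tempting and are not supported.

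- **That the TP-VF association is out of reach.** It is absent only from the specified analyses. TP and VF are scheduled on the same patients at shared visits, so the data will allow it.
- **That the secondary analysis would look the same whether or not TP relates to swallowing.** This is true of the two VF outputs alone. The Pearson analysis of TP with the Hyodo score is not restricted to patients with dysphagia and does inform that question. Its scatterplot would also display individual TP values, but not their VF status.
- **That the schedule contradicts the plan.** Section 2.5.2 says "VF will be conducted before and after RT and at 1, 3, and 6 months after the final date of RT", with no VF during radiotherapy. In section 2.8.2, the reference to each evaluation point is naturally read as each VF visit, and the visit grid in Table 1 is not shown. This is a matter of wording.
- **That a half-width near 6.5 is a property of this trial.** It rests on an SD and a split that the documents do not give.

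**Conclusion.** The point holds for VF. Section 2.8.2, followed as written, gives no TP-VF association, although the abstract and discussion name one as a secondary aim. This conclusion comes from the text and from the fact that a proportion and a one-group mean leave the other group's mean free; it does not depend on the assumed numbers. Those only illustrate the scale: r between about -0.5 and +0.5 is compatible with identical planned outputs, and the missing contrast could be estimated to within about 6.4 to 7.0 at SD 10, or about 9.6 to 10.5 at SD 15, if all 40 are evaluable.

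Severity: should be fixed. The primary endpoint, its analysis and the sample-size reasoning are unaffected.

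**What to change.** In section 2.8.2, or in the analysis plan before the data are analysed:

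1. At each scheduled VF visit, report maximum TP and Hyodo score in participants with and in participants without VF dysphagia, and give the between-group difference in mean TP with its 95% CI. A point-biserial correlation or an area under the ROC curve may be added but is not needed to meet the stated aim.
2. Do the same for change in TP from baseline at the visits after baseline, since the discussion states the aim in terms of change.
3. Write down the rule that classifies a VF examination as dysphagia before analysis. Section 2.5.4 gives none, and both the planned proportion and the added contrast depend on it.

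Cost: no new measurements. It takes a few lines of plan text, agreement on the VF rule, and a small amount of extra analysis. The trial is described as ongoing, with analysis only after the data are fixed, so the change can be made before results are seen.
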